#### Sample size

We will aim to recruit a total of 100 service users and 100 linked caregivers. Assuming 20% attrition, ~40 service users and ~40 caregivers will receive the intervention and each recovery group will have a mean size of 11.4 participants (5–6 service users and 5–6 caregivers). We envisage these are sufficient numbers to adequately assess the acceptability and feasibility of the intervention (Objective 1.a), whilst accounting for potential differences in experience due to variations between clinic catchment areas, e.g. in socio-economic status, accessibility of venue, and community resources.

For the validation of outcome measures (Objective 2.a), we estimate that our final sample size of *n*=80 service users will give >90% power to detect correlations of ≥0.4 and 70% power to detect a standardised effect size of 0.28 for internal sensitivity to change at 2 months compared to baseline. The effect size of 0.28 is based on a mean change of 5 from baseline to follow-up, with a standard deviation of 15 and an intraclass correlation of 0.05. As this is a feasibility study, it is not powered to detect differences in outcome measures between treatment arms (Objective 3.a). We anticipate a total of approximately *n*=4 ASWs, *n*=7 service user facilitators, and *n*=7 caregiver facilitators will be sufficient to make an exploratory assessment of facilitator competence (Objective 1.b).

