Recovery	Recovery Assessment Scale- Domains and Stages (RAS-DS)	The RAS-DS is a self-report measure of mental health recovery [37]. It includes 38 items clustered into four domains of recovery: functional recovery (“Doing things I value”); personal recovery (“Looking forward”); clinical recovery (“Mastering my illness”); and social recovery (“Connecting and belonging”). Each item is rated on a 4-point scale from 1 = “untrue” to 4 = “completely true”. “Percentage scores” are calculated for each domain and an overall score higher score represents more advanced levels of mental health recovery. It has been used previously in clinical settings in South Africa.
Unmet needs	Camberwell Assessment of Need – Short Appraisal Scale (CANSAS)	The CANSAS includes a list of 22 areas considered as potentially important needs for individuals living with mental illness. Each item is rated as either an “unmet need”; “met need” or “no need”. Percentage of unmet needs will be calculated based on number of unmet needs divided by total number of needs identified (unmet needs plus met needs). The scale has been previously used in South Africa [24].
Support for recovery	Brief INSPIRE	The brief INSPIRE assesses recovery support from a worker and has 5 items, each rated 0 “not at all” to 4 “very much”. Responses can be converted to a total score, ranging from 0 (low recovery support) to 100 (high recovery support) [41].
Internalised stigma	Internalized Stigma of Mental Illness (ISMI) Scale	The ISMI-R is a 29-item questionnaire assessing internalised stigma covering four subscales: “alienation”; “stereotype endorsement”; “perceived discrimination”; and “social withdrawal”. Items are scored on a 4-point Likert scale, from strongly disagree to strongly agree. Total scores are calculated by summing the items [38]. The scale has been previously used in South Africa [24].
Perception of respect and value	2 bespoke questions	Two questions “I feel valued and respected by my family” and “I feel valued and respected by my community” will be rated on a 4-point Likert scale, from strongly disagree to strongly agree.
Alcohol use	Alcohol use disorders identification test consumption (AUDIT-C)	The AUDIT-C includes three questions on alcohol consumption, each rated on a 0 to 4 scale. A total score can be calculated. It has been widely used and shown to be useful for assessing alcohol use in the South African context [39].

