##### Quantitative data analysis (outcome evaluation)

The analysis will be completed using Stata 15.0 [34]. Means and standard deviations (or medians with interquartile ranges, where appropriate) will be reported for continuous outcomes and raw counts (number, %) for categorical data. To estimate the potential effect of recovery groups at 2 and 5 months, quantitative outcomes, except Brief INSPIRE, will be compared between treatment arms, adjusting for baseline scores and other predictors, using linear mixed models for continuous variables and generalised linear mixed models for binary variables based on an intention-to-treat analysis; 95% confidence intervals, but not *p* values, will be reported. Adjustment will be made for the within-clinic correlation, and the intracluster correlation will be reported. We will use standard methods for dealing with single missing items from continuous scales, including taking the average across items, or imputing the item [36]. Missing data for other outcomes will not be imputed.

To assess differences in support for recovery between service providers, the paired *t*-test will be used to compare Brief INSPIRE scores amongst intervention arm participants between (i) ASW facilitator support at 2 months and peer facilitator support at 5 months; (ii) ASW facilitator support and psychiatric nurse support at 2 months; and (iii) peer facilitator support and psychiatric nurse support at 5 months. Further analysis may include a linear mixed effects model with scores at all follow-up visits as outcome and scores at the previous time point as predictor. Adjustment will be made for within-clinic correlation.

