#### Assessment of trial procedures

To assess the validity of key outcome measures (Objective 2.a), convergent validity of baseline proxy-reported WHODAS and CANSAS will first be determined by calculating Pearson’s correlation coefficient (*r*). Internal and external responsiveness to change from baseline to 2 and 5 months will be calculated, using proxy-reported WHODAS as an external reference measure. These steps will be repeated for the RAS-DS, using proxy-reported WHODAS as an external reference, and for RAS-DS using CANSAS as an external reference measure. Cronbach’s Alpha will be reported as a measure of internal consistency of the measures. Exploratory Factor Analysis with varimax orthogonal rotation will be conducted to identify any possible factors which the measures may load on.

To assess the feasibility of trial procedures (Objective 2.b), a meeting will be held with ASWs, the social worker, and the study coordinator to gather feedback on the feasibility of the GroupAct and fidelity checklist, e.g., time taken to rate, ease of use, usefulness in providing immediate feedback and identifying training needs. Numbers of eligible participants at each clinic will be compared to predicted numbers (*n*=14) and the proportion consenting to participate will be calculated. The proportion of, and reasons for, participants lost to follow-up at 2 months and 5 months will be recorded. At the 5-month endpoint, all control arm participants will be assessed for contamination including awareness of recovery groups, using a single item administered as the last question on the outcome evaluation assessment. In addition, IDIs will be carried out with control arm participants to gain a more in-depth understanding of extent and means of awareness of intervention groups, and potential impact of exclusion from the groups on their wellbeing (see Table 3). Outcome measure means and standard deviations will be used to inform the sample size calculations for a definitive trial (Objective 2.c).

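### The CANSAS percentage has a denominator that can change after randomisation, so it can rise while needs resolve and is undefined for anyone with no needs

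*Protocol article*

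**What the plan says.** The unmet-needs row of Table 5 describes the instrument: "The CANSAS includes a list of 22 areas considered as potentially important needs for individuals living with mental illness". The response options follow: "Each item is rated as either an “unmet need”; “met need” or “no need". The score is then fixed as a percentage, "number of unmet needs divided by total number of needs identified (unmet needs plus met needs". The article names no count of unmet needs as a companion score and shows no rule for a person with no identified needs.

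The score is used in two places:

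- **Arm comparison (Objective 3.a).** The section Quantitative data analysis (outcome evaluation) compares the arms at both follow-up visits "using linear mixed models for continuous variables and generalised linear mixed models for binary variables based on an intention-to-treat analysis". The baseline value enters the model as well ("adjusting for baseline scores and other predictors"). Beyond single missing items on continuous scales, "Missing data for other outcomes will not be imputed".
- **Validation (Objective 2.a).** The section Assessment of trial procedures correlates baseline CANSAS with proxy-rated WHODAS and examines responsiveness to change. It repeats these steps for the RAS-DS, including "for RAS-DS using CANSAS as an external reference measure".

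The same section uses outcome means and standard deviations to plan the definitive trial (Objective 2.c). The Sample size section says of the arm comparison that "it is not powered to detect differences in outcome measures between treatment arms (Objective 3.a".

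**The concern.** The objectives name unmet needs as the outcome. The score instead measures what share of a person's identified needs is unmet, and that share depends on met needs as well. A met need that ceases to be a need leaves the denominator and pushes the score up, which reads as deterioration. In the other direction, a newly recognised need that is already met pulls the score down, which reads as benefit although no unmet need has gone. A person with no needs has no score at all.

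Three uses are exposed: the sign and size of the exploratory effect estimate for unmet needs, the correlations and responsiveness figures that Objective 2.a must supply, and any mean and standard deviation of this score carried into planning the definitive trial.

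**Working it through.** **Inputs.** From Table 5: 22 areas, three response levels, and score S = 100 × U/(U + M), where U is the number of unmet and M the number of met needs. From the Sample size section: 80 service users after attrition. The article gives no need counts and no rates of change, so any such rates below are assumptions.

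**The plan's own figures.** The only power statement that covers CANSAS is the one for Objective 2.a. With two-sided alpha 0.05 (assumed; none is stated) and n = 80:

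- correlation of 0.4: Φ(atanh(0.4) × √77 − 1.96) = 0.96, against a stated figure above 90%;
- effect size 0.28: Φ(0.28 × √80 − 1.96) = 0.71, against a stated 70%.

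Both reproduce and neither is in dispute. The point concerns the score that goes into those analyses.

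**Step 1: direction of the score.** Start from 6 unmet and 6 met needs.

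| Change | Unmet count | Score |
|---|---|---|
| Start | 6 | 6/12 = 50% |
| 3 met become no need | 6 | 6/9 = 66.7% |
| 1 unmet and 3 met become no need | 5 | 5/8 = 62.5% |
| 2 unmet and all 6 met become no need | 4 | 4/4 = 100% |
| 3 unmet become no need | 3 | 3/9 = 33.3% |
| 3 unmet become met | 3 | 3/12 = 25% |
| All become no need | 0 | 0/0, undefined |

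**Step 2: the general rule.** Suppose a unmet and b met needs become no need, with some needs left and U and M both above 0. The score rises when (U − a)/(U + M − a − b) > U/(U + M). Cross-multiplying gives U × b > a × M, that is b/M > a/U. So the score rises whenever a larger fraction of met than of unmet needs resolves, and it stands still when the fractions are equal.

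The limits of the problem follow from the same algebra. An unmet need that becomes no need never raises the score: it lowers it, leaves it at 100% if there are no met needs, or makes it undefined if it was the only need. An unmet need that becomes met always lowers it. Enumerating all combinations with U + M ≤ 22 confirmed that no unmet-to-no-need step raises the score.

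**Step 3: size under assumed rates.** Take 25% of the 22 items unmet and 25% met, so the expected U = M = 5.5 and the score is 50%.

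- 20% of both kinds resolve: U = 4.4, M = 4.4, score 4.4/8.8 = 50%. The count falls by 1.1 and the score does not move.
- 10% of unmet and 30% of met resolve: U = 4.95, M = 3.85, score 4.95/8.80 = 56%. The count falls and the score rises.
- 20% of unmet become met: U = 4.4, M = 6.6, score 4.4/11 = 40%. Both fall, as they should.

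Simulating 22 independent items gave the same means to within rounding.

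**Step 4: newly recognised met needs.** From 4 unmet and 4 met (4/8 = 50%), two further met needs give 4/10 = 40%, an apparent gain with the same four unmet needs.

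**Step 5: how often the score is undefined.** If items are independent and the mean number of needs is k, P(no needs) = (1 − k/22)^22.

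| Mean needs k | P(no needs) | Expected of 80 |
|---|---|---|
| 2 | 12.3% | 9.8 |
| 3 | 4.0% | 3.2 |
| 4 | 1.2% | 1.0 |
| 6 | 0.1% | 0.1 |

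Correlated items would raise these figures.

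**The case against.** Several points on the other side are sound.

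- **Both arms use the same score.** A reader might infer that the formula biases the arm comparison. The documents do not show this. Bias needs the arms to differ in met-to-no-need movement or in the share of people with no needs, and there are no figures for either. A difference is conceivable: Table 4 lists CANSAS against independence (T7), and referral (P8 in Table 2) could bring met needs to light. But referral and signposting could equally turn unmet needs into met ones, where the score moves correctly.
- **Not every resolved need is misread.** Only the loss of met needs raises the score. This stands, and the point is limited to it.
- **Exclusion of those who improve most is not established.** A reader might infer it from the rule against imputing missing outcomes. That rule speaks of missing data, whereas a person rated no need in all 22 areas has complete data. How 0/0 is scored may be settled in a fuller document not shown. The sample also has psychosis with enduring disability and comes from low-income areas, so people with no needs may be very few.
- **The ratio is a legitimate quantity.** It is the share of identified needs left unmet. That a person with one need and a person with 20 can both score 100% is a property of any percentage.
- **The stakes are limited.** The primary outcomes are acceptability and feasibility. The arm comparison is exploratory, with confidence intervals and no p values. CANSAS is never the only measure for an outcome in Table 4, and RAS-DS is also checked against proxy-rated WHODAS.

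What remains is that the formula is stated in the article, and its behaviour when met needs change follows from it without any person having zero needs.

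**Conclusion.** The point holds as a weakness of a stated scoring rule. As the main score for an outcome called unmet needs, the percentage can rise when the number of unmet needs is unchanged or falling, can stay flat while that number falls, and has no value when there are no needs. It can mislead in the arm comparison and in the Objective 2.a correlations and responsiveness analyses. Since the model adjusts for baseline, an undefined baseline score would be a problem too.

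The direction result is exact and needs no assumptions. The size depends on rates that the article does not give: in the worked case the score moves from 50% to 56% while the mean count falls from 5.5 to 4.95. The undefined-score problem ranges from negligible (mean of 6 needs) to about 10 of 80 (mean of 2), assuming independent items. The documents support saying that the score could bias the exploratory comparison, not that it does. The change is worth making because it is almost free, although the outcome is exploratory.

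**What to change.** In Table 5, make the number of unmet needs (0 to 22) the main CANSAS score. It is defined for everyone with complete items and falls whenever an unmet need is met or resolves. Use it in the arm comparison and in the convergent-validity and responsiveness analyses, including where CANSAS serves as the reference for RAS-DS.

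Report the number of met needs and the total number of needs beside it, so that movement between the three response levels can be seen. Keep the percentage as a secondary descriptive figure among people with at least one need, and give the number of people on whom it is based.

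The items are already recorded, so data collection does not change. The cost is a line or two of wording, one additional reported score, and less direct comparability with any earlier work that used the percentage. Keeping the percentage as a secondary figure limits that loss.

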##### Quantitative data analysis (outcome evaluation)

The analysis will be completed using Stata 15.0 [34]. Means and standard deviations (or medians with interquartile ranges, where appropriate) will be reported for continuous outcomes and raw counts (number, %) for categorical data. To estimate the potential effect of recovery groups at 2 and 5 months, quantitative outcomes, except Brief INSPIRE, will be compared between treatment arms, adjusting for baseline scores and other predictors, using linear mixed models for continuous variables and generalised linear mixed models for binary variables based on an intention-to-treat analysis; 95% confidence intervals, but not *p* values, will be reported. Adjustment will be made for the within-clinic correlation, and the intracluster correlation will be reported. We will use standard methods for dealing with single missing items from continuous scales, including taking the average across items, or imputing the item [36]. Missing data for other outcomes will not be imputed.

To assess differences in support for recovery between service providers, the paired *t*-test will be used to compare Brief INSPIRE scores amongst intervention arm participants between (i) ASW facilitator support at 2 months and peer facilitator support at 5 months; (ii) ASW facilitator support and psychiatric nurse support at 2 months; and (iii) peer facilitator support and psychiatric nurse support at 5 months. Further analysis may include a linear mixed effects model with scores at all follow-up visits as outcome and scores at the previous time point as predictor. Adjustment will be made for within-clinic correlation.

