### Study design

The design is an individually randomised parallel group feasibility trial comparing recovery groups in addition to TAU compared to TAU alone in a 1:1 allocation ratio (see Fig. 1). We will use mixed methods to address our study objectives. Data will be collected at baseline, 2 months, and 5 months post-intervention start.

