#### Recovery groups: design and overview

A theory of change map (Additional file 1) was developed during the formative phase as a model for explaining how the PRIZE intervention might facilitate and support psychosocial recovery [28]. The PRIZE theory of change map indicates (i) Participant outcomes: aspects of recovery deemed to be both important to service users and caregivers, and achievable through recovery groups, and (ii) Preconditions: aspects of participant engagement with, and delivery of, recovery groups theorised as necessary to attain the desired outcomes. The recovery group intervention, training, and supervision was designed to achieve the theory of change preconditions and outcomes. The intervention arm will comprise seven recovery groups, each linked to a clinic catchment area and comprising both service users and caregiver participants. Recovery groups will be delivered in two phases: a 2-month phase facilitated by an auxiliary social worker, then a 3-month peer-led phase.

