### Assignment of interventions

The randomisation code will be generated by an independent statistician using permuted block randomisation. The randomisation will be stratified by clinic catchment area. The trial social worker will supply the study coordinator with the details of all recruited participants, including study ID. For each recruited participant, the study coordinator will determine the allocation code using the Redcap randomisation module. They will then inform the participant of the trial arm to which they have been allocated (TAU or TAU + recovery groups) by telephone. The trial social worker and assessor will be informed of the participant ID number prior to baseline data collection, but will be masked to allocation status. At the 5-month study endpoint, assessors will be asked to report whether they have been unmasked to allocation status. Data analysts will also be masked to allocation status. Due to the nature of the intervention, it is not possible to mask participants or interventionists (ASWs or social workers).

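### The between-arm models name clinic as the only clustering unit, so variation between recovery groups, which exist in one arm only, is not represented in the arm contrast and its 95% intervals may be too narrow.

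*Protocol article*

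**What the plan says.** The Study design section of the Protocol article states that individuals are randomised: "The design is an individually randomised parallel group feasibility trial comparing recovery groups in addition to TAU compared to TAU alone in a 1:1 allocation". Under Assignment of interventions, "The randomisation will be stratified by clinic catchment area", so each clinic area contributes participants to both arms. Treatment is delivered in groups in one arm only (Recovery groups: design and overview): "The intervention arm will comprise seven recovery groups, each linked to a clinic catchment area and comprising both service users and caregiver participants". TAU participants belong to no group.

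Quantitative data analysis (outcome evaluation) plans linear mixed models for continuous outcomes and generalised linear mixed models for binary ones. They are adjusted for baseline and other predictors, by intention to treat, and reported with 95% confidence intervals and no p values. On clustering it says only: "Adjustment will be made for the within-clinic correlation, and the intracluster correlation will be reported".

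For the definitive trial's sample size (Objective 2.c), Assessment of trial procedures says: "Outcome measure means and standard deviations will be used to inform the sample size calculations for a definitive trial". No ICC is listed there.

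**The concern.** This is a partially nested design: intervention participants are clustered in recovery groups, and controls are not clustered by treatment. Two sources of correlation have to be kept apart.

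- **Clinic.** People from the same catchment area resemble each other whichever arm they are in. Because both arms are present in every clinic, this effect cancels from the within-clinic difference between arms.
- **Recovery group.** Members of one group may become alike because they share sessions, facilitators and each other's input. This affects one arm only, does not cancel, and adds to the variance of the treatment effect.

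The article names the first source and not the second. Group effects are plausible here: members generate much of the session content, choose their own peer facilitators and direct the move to the peer-led phase.

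Two things are at stake. The intervals are the only inferential output of the arm comparison. And the trial's stated aim includes finding key parameters for a definitive trial; if that trial keeps individually randomised group treatment, the group ICC is one of those parameters.

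**Working it through.** **Inputs from the article.** Seven groups, one per clinic area. Recruitment (Sample size): "We will aim to recruit a total of 100 service users and 100 linked caregivers". Group size (Sample size): "Assuming 20% attrition, ~40 service users and ~40 caregivers will receive the intervention and each recovery group will have a mean size of 11.4 participants". This gives m = 40/7 = 5.71 service users per group, and the same for caregivers if each has one linked caregiver. Both together give 80/7 = 11.4, which matches the article.

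**Assumed.** The group ICC, ρ, taken over 0.01 to 0.20, and equal total variance in the two arms.

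**The one stated figure that uses an ICC.** Sample size claims "70% power to detect a standardised effect size of 0.28 for internal sensitivity to change at 2 months compared to baseline", with n = 80. The check is Φ(√80 × 0.28 − 1.96) = Φ(0.544) = 70.7%, or 69.6% with the noncentral t, so 70% reproduces. The 0.28 is derived from a change of 5, an SD of 15 and an ICC of 0.05. Solving (5/15)/√(1 + (c − 1) × 0.05) = 0.28 gives a cluster size c of about 9.3. A cluster of 80/7 = 11.4 would give 0.270 instead. The cluster unit is not named, so this 0.05 cannot be read as a stated recovery-group ICC. The calculation also concerns change over time, not the arm contrast.

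**Effect on the arm contrast.** With the shared clinic effect cancelled:

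- design effect in the intervention arm: DE = 1 + (m − 1)ρ
- true SE / SE without a group term: √((1 + DE)/2)

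| Assumed ρ | DE | SE ratio |
|---|---|---|
| 0.01 | 1.047 | 1.012 |
| 0.05 | 1.236 | 1.057 |
| 0.10 | 1.471 | 1.112 |
| 0.20 | 1.943 | 1.213 |

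With no attrition (m = 50/7 = 7.14) the ratios at 0.01, 0.05 and 0.10 are 1.015, 1.074 and 1.143.

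**Simulation.** Seven clinics, 40 per arm, 2,000 runs per setting, REML, z intervals. Each cell gives the result with a true clinic ICC of 0 / 0.05.

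| Group ICC | Coverage, clinic intercept only | Mean reported ICC, clinic intercept only | Coverage with group term added |
|---|---|---|---|
| 0 | 94.6% / 94.3% | 0.021 / 0.056 | 95.3% / 95.1% |
| 0.05 | 93.2% / 93.0% | 0.027 / 0.064 | 94.9% / 94.6% |
| 0.10 | 91.3% / 90.9% | 0.036 / 0.074 | 93.4% / 93.4% |
| 0.20 | 87.9% / 87.4% | 0.050 / 0.098 | 92.7% / 92.5% |

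Using t on 6 degrees of freedom with the group term gives 97% to 99%, which is conservative.

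**Why the reported ICC moves so little.** Each clinic has about 11.4 service users, hence 11.43 × 10.43/2 = 59.6 pairs. Of these, 5.71 × 4.71/2 = 13.5 pairs, or 23%, are both in the intervention arm. With no clinic effect, the reported value averages 0.036 when the group ICC is 0.10. With clinic and group ICCs of 0.05 each, members of one group correlate at 0.10 in total, and the reported value averages 0.064. It separates neither component.

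**What the group ICC would mean for planning.** If a definitive trial kept this design and group size, n per arm would be multiplied by (1 + DE)/2, which is 1.118 at ρ = 0.05 and 1.236 at ρ = 0.10. This factor does not depend on the target difference or the SD.

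**The case against.** **The exact random-effects structure may be in an analysis plan that is not shown.** Mixed models with a clinic-level random coefficient for arm would be compatible with the wording, and would cover the gap. That is why the size above is tied to the random-intercept reading. The objection does not remove the point, because the article is not silent: it names clinic as the adjustment and one ICC as the output.

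**Group clustering is not wholly ignored.** A reader might infer that it is. With one group per clinic, clinic and group coincide within the intervention arm, so a clinic term absorbs part of the group correlation. What is missing is the arm-specific part, and that is the part which enters the contrast.

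**The plan does not send a wrong ICC to the definitive trial.** A reader might infer this too. Objective 2.c names only means and SDs as inputs; the ICC is merely reported. Nor is the future design settled, since Objective 2.b asks whether individual randomisation is suitable. Under a clinic-randomised design, clinic-level correlation would matter.

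**The stakes are limited.** The primary outcomes are acceptability and feasibility, assessed by qualitative work and descriptive indicators. The arm comparison is exploratory and expressly not powered, and the article ties no decision to its intervals. This stands, and it lowers the priority.

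**Seven groups support only a weak estimate.** By one-way ANOVA on 6 and 33 degrees of freedom, with a true ICC of 0.05, the group variance is estimated at or below zero in about 40% of trials. A typical 95% interval for the ICC runs from below zero to about 0.49. This also stands, and the change proposed below has to allow for it.

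**Conclusion.** The point holds in a limited form. The clustering adjustment named in the article does not represent correlation from group treatment in one arm. If it is fitted as a clinic random intercept, the intervals for the arm contrast are too narrow whenever the group ICC is above zero: negligibly at 0.01, modestly at 0.05 and more clearly at 0.10. The single ICC cannot be read as the recovery-group ICC.

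This rests on the random-intercept reading, on about 5.7 members of each type per group, and on a group ICC that the documents do not supply. It should be put right before analysis, but it does not touch the trial's primary conclusions.

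**What to change.** Change the analysis wording as follows.

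1. Keep clinic in the model as the stratification factor, and add a recovery-group (clinic-by-arm) random effect in the intervention arm only.
2. For the linear mixed models, use small-sample degrees of freedom (Satterthwaite or Kenward–Roger). These do not carry over to the binary models, whose intervals should be described as approximate.
3. Report the intervention-arm group ICC with its confidence interval, separately from any clinic ICC.
4. Under Objective 2.c, list that group ICC beside the SDs, for the case where the definitive trial keeps individually randomised group treatment.
5. Because the group variance may be estimated at zero, show a sensitivity interval over a stated range of assumed group ICCs, for example 0.01 to 0.10.

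No extra data or participants are needed. The cost is somewhat wider intervals and an ICC that seven groups can estimate only roughly, so it should inform planning and not settle it.
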